## Home Visit

Intervention participants will have a home visit from the trial nurse booked within 7 days of hospital discharge. At this point the care plan is further discussed with the patient and interventions agreed upon with the patient. The home visit is an opportunity to increase rapport and develop your clinical relationship and trust, to assess patient risk, and assess their physical state and symptoms after discharge from hospital. Although some issues such as medication management can start to be addressed in hospital, it is only at the home visit that the nurse can really assess how the participant manages their medications. The home visit will only be provided to patients in the Metropolitan area.

Prior to the home visit, ensure you complete your site’s home visit risk assessment form as local protocol requires. If the risk assessment shows unacceptable risk the visit is not to take place and the home visit procedures conducted over the phone.

If risk is acceptable, at the home visit, complete the ALFIE Study home visit form. It is envisaged that the home visit will take 30-60 minutes. Time the visit and enter the duration of the visit on the Home Visit form (Appendix I). Complete a full report of the visit in the participant’s case note as a record of your findings and to record the plan.

## Telephone Contact

Patients in the intervention group receive (at least) weekly telephone calls for the first 3 months. Ensure all patient contacts are recorded in the patient contact log (Appendix M). There is a window of +/- 2 days for all patient contacts.

## Outpatient review by Specialist Gastroenterologist/Hepatologist

Review by a specialist must be scheduled within 1 month (4 weeks) of discharge from hospital for all patients in the intervention group. The nurse must attend this appointment with the patient. In preparation for the outpatient appointment the following should be updated:

- - Medication list
  - Care Plan
  - Ensure screening and surveillance requirements are up to date (or booked)

At this appointment the specialist will discuss the care plan with the nurse and the patient and sign off on the care plan.

## Month 3, Month 6, Month 12, Month 18

Patients in the intervention group have their Child Pugh and Meld scores completed at 3, 6, 12, 18 months and at end of trial (Appendix N). Collect the information from the most recent bloods taken as part of usual care, the patient will not be required to have a blood test taken just for this score to be done.

Surveys are due for both groups at this time. For intervention patients this should ideally be scheduled at the same time the specialist outpatient appointment is scheduled to enable accurate determination of the Child Pugh and MELD score. Ensure the contact log is up to date. Patients will be provided the option of receiving the surveys via standard post or electronically, via email, at consent.

Record hospital and liver-related outpatient admissions/attendances/non attendances at the month 12 visit.

## End of Study

Patients will have an end of study visit at withdrawal, when listed on the transplant waiting list, or at the end of the study (24 months after the randomisation of the first patient).

Both groups will have the following collected:

- Cirrhosis Knowledge Assessment Questionnaire
- Ask 12
- CLDQ
- EQ-5L-5D
- PIH Scale
- Patient Satisfaction Questionnaire
- Resource use questionnaire
- MBS and PBS information (to be collected centrally by the coordinating site) if the patient signed the consent form at the beginning of the trial.

Please remind the participant that a member of the study coordinator team may be in contact via telephone to ask a few questions about their experiences but they can refuse to participate if they wish. Thirty two patients will be consecutively recruited (8 patients per site, 4 patients from each study arm) for the telephone interviews.

The following will also be completed/updated at end of study in both groups:

- Hospital admissions log
- Outpatient attendance log
- Concomitant medications
- Comorbidities list
- Child Pugh & MELD score
- HCC assessment
- Ascites and HE assessment
- Osteoporosis assessment
- Alcohol assessment
- Variceal assessment
- Nutrition assessment

It is preferable that the information is collected face-to-face as the control group patients can have some education about their liver disease if they wish. Ensure they receive the Cirrhosis Booklet.

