# Planned Timeline

April 2020

April 2022

September 2018

First patient randomised

Last patient randomised

EOT

Intervention starts

Intervention ends

Each patient will receive 24 months of intervention will be different for each patient.

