## Study duration

At each site, recruitment will occur for 12-18 months, and then the trial will continue until the last participant recruited has had 24 months of CDM (total 3-year study duration).

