# Intervention and Implementation

The term ‘intervention’ refers to the Chronic Disease Management model applied to the care of the patient with cirrhosis of the liver. The intervention starts after randomisation and will continue until the end of the study which is 24 months after the first randomised patient.

Randomisation signals the start of the treatment period. Every Participant will have at 24 months of intervention.

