## Control/usual care group

Control/usual care patients will continue hospital and out of hospital management via usual care processes. To prevent contamination of usual care patients by the intervention, usual care patients will have no contact with CLD nurses until a final end of study interview. Usual care patients will be mailed surveys at baseline, 3 months, 6 months, and then 6-monthly until the end of the trial (24 months after the first patient randomised). At the end of the trial, control group participants are invited for a face-to-face review to complete the surveys, are given the Cirrhosis Booklet and offered an education session.

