## Intervention period

Patient recruitment will occur during a 12-18 month window and the intervention will occur for 24 months for each patient. In the case of patient death, liver transplantation and loss to follow up, the study will end.

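### Three sections close the study 24 months after the first randomisation while others give every participant 24 months; under the first rule, 12 to 18 months of recruitment cuts scheduled person-time by 25% to 37.5%

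*Protocol*

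**What the plan says.** Three sections of the protocol fix a common closing date, counted from the first randomisation:

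- *Intervention and Implementation*: the intervention "will continue until the end of the study which is 24 months after the first randomised patient".
- *Control/usual care group*: surveys are mailed "until the end of the trial (24 months after the first patient randomised").
- *End of Study*: the final visit falls at withdrawal, at transplant listing, or "at the end of the study (24 months after the randomisation of the first patient"). Its assessments apply to both groups.

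Other places give each participant 24 months:

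- *Study duration*: "the trial will continue until the last participant recruited has had 24 months of CDM (total 3-year study duration").
- *Intervention period*: "the intervention will occur for 24 months for each patient".
- *Planned Timeline*: "Each patient will receive 24 months of intervention".
- *Intervention and Implementation* itself, in its second paragraph: "Every Participant will have at 24 months of intervention".
- The activity schedules for control and intervention patients, which count visits from randomisation (from Month 3 on) up to a Month 24/EOS column.

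*Study duration* and *Intervention period* put recruitment at 12 to 18 months. *Sample size and power analysis* uses neither rule explicitly; it assumes a median follow-up of 18 months.

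**The concern.** The two rules agree only for the first patient randomised. For everyone else the first-patient rule gives a shorter follow-up, and the shortfall grows with the date of entry.

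The primary outcome is a rate of unplanned liver-related admissions, so the closing date bounds its exposure time. The end-of-study visit triggers the final hospital admission log, and the second review period on that form (Appendix J) runs from 12 months to a trial end that depends on which rule is applied. The same date decides who contributes Month 12, 18 and 24 surveys to the quality-of-life and QALY analyses. Site staff schedule from the sections that carry the conflict.

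**Working it through.** **Inputs.** Recruitment R = 12 to 18 months (*Study duration*, *Intervention period*). Usual-care rate 3 per person-year, 20% reduction (so 2.4), total N = 146, 80% power, α = 0.05, 20% attrition, median follow-up 18 months (*Sample size and power analysis*). Allocation 1:1 (*Trial design*). Assumed because not stated: two-sided test, Poisson variance, uniform accrual.

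**1. The plan's sample size.** With follow-up t in years:

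n per arm = (1.960 + 0.842)² × (1/3 + 1/2.4) / t / (ln 0.8)² = 7.849 × 0.75 / (0.0498 t)

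- t = 1.5 (the written 18 months): 78.8 per arm, so 158 in total, or 2 × 78.8 / 0.8 = 198 with attrition. Neither is close to 146.
- t = 2.0: 59.1 per arm, and 2 × 59.1 / 0.8 = 148 with attrition. This is close to 146.
- One other combination comes near: a one-sided test at 18 months with attrition as N × 1.2 gives 149.

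**2. Follow-up under the first-patient rule.** A participant entering at month e has 24 − e months. With uniform accrual over R months, mean and median follow-up are both 24 − R/2, and the shortest is 24 − R. The share that cannot reach Month 12 is (R − 12)/R, and the share that cannot reach Month 18 is (R − 6)/R.

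| | R = 12 | R = 18 |
|---|---|---|
| Shortest follow-up (months) | 12 | 6 |
| Mean and median follow-up (months) | 18 | 15 |
| Loss against 24 months each | 6/24 = 25% | 9/24 = 37.5% |
| Loss against the 18-month median | 0% | 3/18 = 17% |
| Cannot reach Month 12 | 0% | 6/18 = 33% |
| Cannot reach Month 18 | 6/12 = 50% | 12/18 = 67% |

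**3. Sensitivity of the loss against 24 months each** (R = 12 and R = 18).

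- Exponential attrition of 20% by month 24: 23% and 35%.
- Two-year survival of 60% (the Child Pugh B figure in *Background*): 21% and 33%.
- Two-year survival of 35% (the Child Pugh C figure): 17% and 28%.
- Front-loaded accrual, no attrition: 17% and 25%. Back-loaded: 33% and 50%.

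**4. Power with 146 randomised.** After 20% attrition 146 × 0.8 / 2 = 58.4 per arm remain. SE = √(0.75 / (58.4 t)), and power = Φ(0.2231/SE − 1.960).

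| Follow-up | SE | Power |
|---|---|---|
| 24 months each | 0.0801 | 79.5% |
| 18 months | 0.0925 | 67% |
| 15 months | 0.1014 | 60% |

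The planned negative binomial analysis allows for over-dispersion, which would lower all three figures. The protocol states no dispersion value.

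**5. Which rule the protocol's dates fit.** *Planned Timeline* carries September 2018, April 2020 and April 2022. Their order and labels have to be inferred from figure text. Read as first randomisation, last randomisation and end, they give 19 months of accrual and then 24 months. The first-patient rule would close the trial about September 2020. Patient interviewees are invited at their end-of-study visit, yet the two interview blocks run from October 2020 to February 2021 and from October 2021 to February 2022, both after that date. These dates fit the per-participant reading.

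**The case against.** The strongest reply is that the schedules, the timeline and the interview blocks already show how the trial was meant to run. On that view the first-patient wording is residual, and few patients would actually be cut off. This has force: the person-time loss is what follows if the rule is applied, not an expected loss. It does not remove the conflict, because the wording appears in three operative sections and one of them contradicts itself.

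Four stronger readings are tempting, and the protocol does not support them.

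- **Controls stopped earlier than intervention patients.** A reader might infer this because the usual-care section carries only the first-patient rule. That sentence concerns mailed surveys. The control schedule also runs from randomisation to Month 24/EOS, and *End of Study* covers both groups, so the conflict affects both arms alike.
- **The whole loss as a shortfall against the power calculation.** The protocol powers on a median of 18 months, which is exactly what the first-patient rule gives with 12 months of uniform accrual. The 67% at 18 months is what 146 patients give under the protocol's own written inputs; it is a defect of the sample-size section, not an effect of the closing rule.
- **A loss of 40%.** This needs 19 months of accrual (9.5/24 = 39.6%, or about 38% with 20% attrition), which rests on the inferred timeline dates. The stated window gives at most 37.5% under uniform accrual.
- **The three-year total as plainly wrong.** It holds at 12 months of recruitment (12 + 24 = 36 months). It fails for longer recruitment: 18 + 24 = 42 months.

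**Conclusion.** The contradiction stands and has to be resolved, because it leaves the exposure window of the primary outcome open to two readings. Under the first-patient rule the last recruit has 6 to 12 months instead of 24, and scheduled person-time falls by 25% to 37.5%. That range assumes uniform accrual over the stated window and no attrition; with 20% attrition it is about 23% to 35%. Against the 18-month median in the sample-size section the loss is 0% to 17%.

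The basis of the power figure is itself unclear. Under a two-sided Poisson calculation with attrition handled as N/(1 − 0.2), 146 patients give about 80% power only with 24 months each. The follow-up written in that section gives about 67%.

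**What to change.** - Reconcile *Intervention and Implementation*, *Control/usual care group* and *End of Study* with *Planned Timeline*, *Study duration*, *Intervention period* and the two activity schedules.
- State one end of follow-up and data collection, identical in both arms. The protocol's own schedules and dates point to 24 months after each participant's randomisation, with the trial closing when the last participant reaches it.
- Define trial end on the Appendix J admission log to match.
- For how long the intervention itself is delivered, the sponsor must reconcile the sections; this review does not choose between them.
- Align the three-year total with the recruitment window.
- Restate follow-up and power in *Sample size and power analysis* on the same basis, naming the sidedness of the test and how attrition enters.

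The cost is a wording amendment in a few sections and one recalculation. The protocol shows no budget, so any effect on resources cannot be judged from it.

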# Qualitative Analysis : Patients and Staff

A qualitative analysis of the patients’, nurses’ and doctors’ perceptions of the ALFIE trial is essential to assess the efficacy of the trial and to improve the delivery of the intervention according to their needs.

The primary aim of this qualitative review is to understand more about the actual conduct of the trial, the issues, challenges and learnings; to understand how and why the implementation achieved what it did. Secondary aims are to:

1. Analyse the patients’ experience in the ALFIE trial from the perspective of patient satisfaction, education and facilitation of self-management.
2. To determine the satisfaction of the CLD nurses and hepatologists involved in implementing the intervention.

An inductive, descriptive qualitative study design with qualitative interviews has been chosen for this qualitative review.

## Number of participants

Thirty two patients will be consecutively recruited over two five month periods — October 2020 to February 2021 (block 1) and October 2021 to February 2022 (block 2). Each site will aim to recruit 8 patients in total, with 4 patients from each study arm.

Seven nurses and five hepatologists will be approached for participation at the end of the study.

## Recruitment and consent process

Patients: Informed consent for the interviews was obtained during consent into the study, but patients will be provided the option of being contacted or not. Potential participants will be invited to take part in the telephone interview by their CLD nurse during their end of study visit and will obtain consent for the designated interviewer from FMC to contact them. The CLD nurse will inform the patient that the interview will take approximately 20 minutes and will involve briefly talking about their experience being involved in the ALFIE trial. If the patient consents, the CLD nurse will pass on their name and contact details to the designated interviewer. The designated interviewer from FMC will then contact the patient to conduct the interview. The participant will be advised that they can change their mind and cancel the interview if they wish.

Staff: The designated interviewer from FMC will email staff participants with the information sheet and request a convenient time to conduct the interview. As all interviews will be conducted over the phone, the staff participant will respond with email consent if they are interested in participating and will have seven days to consider participation. Upon consent, staff participants will be provided the interview questions 1 day prior to the interview, to ensure that they have sufficient time to consider their answers. The participant will be advised that they can change their mind and cancel the interview if they wish.

## Data collection, storage and analysis

All interviews will be conducted over the phone. The interview will be audio-recorded and transcribed verbatim, and field notes will be taken during and after each interview. One researcher, a registered nurse and not part of the core research team, will conduct all the interviews. The designated interviewer will be provided a set of standardised questions to ask the patients (Appendix V) and staff (Appendix W) during the interview. The interviews will be open ended and carried out as a conversation to understand the participant's experience with the ALFIE trial. For the patient interviews, the designated interviewer will be blinded to the patient’s randomisation group and treating hospital.

Recordings of interviews will be allocated a unique study ID prior to being sent for transcription. All data will be assigned a unique study ID and will be stored securely, in a password protected computer and only FMC study investigators will have access to the data. Hardcopies of the transcriptions will be kept in a secure locked filing cabinet in the Hepatology Department research office at FMC. Participants will be given the option of requesting the transcript to check their answers.

A qualitative approach will be used to analyse the collected data as described in grounded theory. This approach for content analysis is interpretive in nature and used to describe or illuminate a phenomenon through identification of manifest (the obvious) and latent (underlying meaning) content in a text. This will involve: (1) reading of the text several times to become familiar with it and reflect upon the content, (2) identification in the text of meaning units that describe the phenomenon, (3) meaning units condensed and essential content is abstracted and labelled with a code, and (4) codes compared based on similarities and differences sorted into themes. Coding and sorting of themes will be assisted using the analysis took NVivo.

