## Appendix V – ALFIE Interview Questions for Patients

Introduction

Hi, I’m XX. Thank you for your time today. I am not a member of the ALFIE trial but have been asked to assist the research team with conducting these phone interviews. The aim of this interview is to find out about your experience being part of the ALFIE trial.

Questions

1. Tell me about your experience of having your liver disease managed at <your hospital>.
2. Was anyone involved in your care besides doctors?
3. Did you have a special liver nurse in charge of your care?
4. If yes, could you tell us about your experience receiving care from this liver nurse?
5. Did you feel supported during your treatment?
6. Did you receive any education about your liver disease?
7. Did you learn about self-management for the complications of your liver disease?
8. Do you feel confident about receiving appropriate care for your liver disease?
9. What were some of the good things about the care you received for your liver disease?
10. Do you have any complaints about the care received?
11. Is there anything that would have made the care you received for your liver disease any better?
12. Do you have any other feedback about the care you received by the liver department at <your hospital>?

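### The patient interviewer is described as blinded to arm and hospital, but questions 2–4 of the interview script will usually reveal the arm before questions 5–12 are asked

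*Protocol*

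**What the plan says.** The Qualitative Analysis part of the protocol plans telephone interviews with patients from both arms. Under Data collection, storage and analysis, one researcher from outside the core team conducts them all, as open-ended conversations. For the patient interviews, "the designated interviewer will be blinded to the patient’s randomisation group and treating hospital". No end point or qualification is attached to that statement.

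The same section ties the interviewer to a fixed script: "The designated interviewer will be provided a set of standardised questions to ask the patients (Appendix V) and staff (Appendix W) during the interview". In Appendix V, question 1 is "Tell me about your experience of having your liver disease managed at <your hospital>". Question 2 asks whether people other than doctors were involved. Question 3 is "Did you have a special liver nurse in charge of your care" and question 4 is "If yes, could you tell us about your experience receiving care from this liver nurse". Questions 5–12 deal with support, education, self-management, confidence in care, good points, complaints, possible improvements and other feedback. The last of them is "Do you have any other feedback about the care you received by the liver department at <your hospital>".

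On referral, the Recruitment and consent process section says that, if the patient agrees, "the CLD nurse will pass on their name and contact details to the designated interviewer". On the control arm, the Control/usual care group section says that "usual care patients will have no contact with CLD nurses until a final end of study interview".

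**The concern.** The protocol states a design property, a blinded interviewer, and prescribes a script that tends to remove it. No slip by patient or interviewer is needed; asking the questions in the printed order is enough.

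What is at stake is interviewer bias in the qualitative work. One person does every interview in conversational form, so knowing the arm can influence which answers are probed and how. The topics most open to that influence, such as support, education, self-management and complaints, come after the disclosure. They are also close to the stated secondary aim of analysing patients' experience in terms of satisfaction, education and self-management. If a report repeated the blinding statement as it stands, readers would credit the interviews with more protection than they had.

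**Working it through.** No statistical calculation applies. The check sets the sections side by side and counts.

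**1. Number of interviews.** Under Number of participants (Qualitative Analysis), each site aims for 8 patients, 4 from each arm. With the 4 sites given under Participant Population:
- 8 × 4 = 32 interviews, which reproduces the protocol's figure;
- 4 × 4 = 16 per arm.

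**2. Does question 3 identify the arm?**
- The Chronic Disease Management Model and Role of CLD nurse sections build the intervention around the chronic liver disease (CLD) nurse: home assessment, care plan, weekly calls, reminders and a direct telephone line.
- Participant Population says the model was not in use at the participating sites, so a yes to question 3 is unlikely to reflect routine care.
- Control/usual care group excludes nurse contact for controls until the closing interview, so a control patient would usually answer no.

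A yes therefore points strongly to intervention and a no to control. The marker is strong but not perfect. Patients are invited to the interview at the end-of-study visit, where controls may meet the nurse, receive the booklet and be offered education. A control patient could have that nurse, or another nurse, in mind.

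**3. What is asked before and after the disclosure?**

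| Question(s) | Subject | Position |
| --- | --- | --- |
| 1 | Open question on experience of care | Before |
| 2–4 | Other staff, liver nurse, experience of that nurse | The disclosing block |
| 5–12 | Support, education, self-management, confidence, good points, complaints, improvements, other feedback | After |

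The questions put to every patient after the block number 12 − 4 = 8 of 12. Counting the conditional question 4 as well, 12 − 3 = 9 come after question 3. One question about experience, question 1, comes before it.

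**4. Does the interviewer learn the hospital?** There are two routes.
- Questions 1 and 12 carry a bracketed field. Filled in, it names the hospital. Read aloud as printed, it does not.
- The CLD nurse makes the referral, and the Training section under Trial Management places the CLD nurses at four named hospitals. An interviewer who knows which nurse referred the patient can infer the site. The protocol says that name and contact details are passed on; it does not say that the hospital is.

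Disclosure of the hospital is therefore plausible by either route, but the text does not make it certain.

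**The case against.** The strongest reply is that *blinded* here may mean only that nobody tells the interviewer the arm or hospital. The script fits that reading: questions 3 and 4 are worded for someone who does not know the answer. Not knowing the arm before the call and during question 1 is also some protection. This stands in part, and it is why the point concerns the scope of the statement and not its complete absence. It does not rescue the statement as written, which has no end point.

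A reader might also infer four stronger things that the documents do not support.

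- *Every interview is unblinded.* Question 3 is not a perfect marker of arm, so *usually* is as far as the text goes.
- *The script requires the hospital to be named.* It prints a placeholder that can be read neutrally, and disclosure through the referring nurse is an inference.
- *A between-arm comparison will be wrongly reported as blinded.* Sampling is balanced by arm, which invites comparison. However, the design is described as inductive and descriptive, no formal contrast between arms is planned, and nothing says the interviews will be reported as blinded. Satisfaction, self-management and knowledge are measured separately by survey.
- *Coding should be masked by removing the liver-nurse text from transcripts.* The protocol claims no masked coding, so nothing is contradicted. Removing that text would also work against the aim of understanding how and why the implementation achieved what it did.

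Finally, reordering the script cannot guarantee the blind, because patients may mention the nurse in answer to question 1. That is correct and limits the benefit of the fix.

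**Conclusion.** The point holds in a limited form. The protocol states without qualification that the patient interviewer is blinded to arm and hospital. Its own script will usually disclose the arm at questions 2–4, ahead of 8 of the 12 questions, and the hospital may also become known.

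This rests on two assumptions: that the interviewer follows the printed order, and that most patients understand question 3 as referring to the trial's nurse. Both are reasonable on the text.

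The reach is small: up to 32 descriptive interviews, 16 per arm. The primary outcome, unplanned liver-related admissions, and its analysis are untouched. It is a worthwhile, low-priority correction.

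**What to change.** - **Appendix V:** move questions 2–4 to the end. Nine questions (1 and 5–12) would then precede the disclosing block, instead of one.
- **Questions 1 and 12:** drop the brackets and use the neutral words *your hospital*.
- **Data collection, storage and analysis:** restate the blinding along these lines: *the interviewer is not informed of arm or hospital before the interview; arm may become known during it.* Do not report the interviews as fully blinded.

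The cost is an edit to a short script and one sentence of the protocol. The content of the questions is unchanged apart from the neutral hospital wording, and no extra data are collected. The remaining weakness is that patients may raise the nurse unprompted and the referral may still suggest the site, so the blind stays partial. The protocol would then describe it accurately.
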